**Figure 1 figure1:**
[figure not shown]
Mean daily glycemic index (GI) and glycemic load (GL) calculation.

#### Secondary Outcomes

Secondary outcome measures, including GI knowledge and skills, self-efficacy, body mass index (BMI; weight and height), waist circumference, clinical measures (glycated hemoglobin [HbA_1c_], systolic blood pressure, total cholesterol, and high-density lipoprotein), and computer proficiency were assessed at the baseline and at 3 months after completing the intervention. In addition, demographic data were collected.

#### Glycemic Index Knowledge and Self-Efficacy Assessment

Pre- and postintervention GI concept knowledge and self-efficacy were assessed and quantified using the Glycemic Index Foods Quiz from a previous study [45]. Dietary data from a previous intervention within the same population showed that, out of 196 participants, 16% were not familiar with low-GI eating and 28% did not include low-GI foods in their diets [46]. About 35% (70/199) indicated that they did not know about GI, and of those who claimed the knowledge of GI, only 34% reported choosing low-GI foods for >6 months in another study [47]. These corroborate previous findings in which only 38% of people with diabetes received nutrition therapy across Canada [28] with <40% of dietitians including the GI concept in T2D dietary self-care counseling [26,27]. Overall dietary self-care behavior was assessed using dietary items in the validated and widely used Summary of Diabetes Self-care Activities measure [48]. The Glycemic Index Foods Quiz, therefore, enabled assessment of the net change in GI knowledge and self-efficacy due to the intervention.

#### Clinical and Anthropometric Measures

Clinical outcome measures included HbA_1c_, systolic blood pressure, and lipid profile. Capillary blood samples (35 μL) were collected from participants to assess HbA_1c_ value using previously validated point-of-care testing device for HbA_1c_ (DCA Vantage) [49] and lipid profile (Cholestech LDX). Systolic blood pressure was measured according to the standard protocols using (BPTru) [50].

In addition, weight, height, and waist circumference were assessed according to the Canadian Physical Activity, Fitness and Lifestyle Appraisal procedures [51]. Body weight in kilograms (kg) and height in meters (m) were measured for each subject in light clothing and with no shoes on. Body weight was measured to the nearest 0.1 kg with a portable digital scale (Tanita BWB-800S, Arlington Heights, IL, USA), and height was measured using a portable stadiometer (Tanita HR-100). Waist circumference was measured to 1 mm at the top of the iliac crest using a spring-loaded Gulick anthropometric tape (FitSystems Inc, Calgary, AB, Canada). Regular, monthly quality assurance checks were conducted on the point-of-care devices and scale.

#### Physical Activity

Self-reported physical activity was assessed using the Godin Leisure Time Exercise Questionnaire [52]; the validity of this questionnaire is well established [53], and data suggest that self-reported physical activity estimates function as a suitable predictor of future behavior [54]. Participants were asked to report the frequency and duration of light-, moderate-, and vigorous-intensity leisure-time physical activity that lasted at least 10 minutes over a typical week during the past month. The number of weekly minutes for each intensity level was calculated by multiplying the frequency of activity by the duration in minutes. The sum of weekly minutes of moderate-to-vigorous physical activity (MVPA) gave the total MVPA minutes per week.

#### Computer Proficiency

Participants’ computer proficiency was measured using the Computer Proficiency Questionnaire (CPQ) at baseline and 3-month postintervention. The CPQ was developed for evaluating the competencies of seniors with regards to use of computers and associated applications such as the internet [55]. The CPQ assesses competence across 6 different subscales: computer basics, printing, communication, internet, scheduling software (calendar), and multimedia use (entertainment) for gauging an individual’s specific and overall computer proficiency.

#### Sociodemographic Covariates

Demographic information including age, sex, marital status, education, employment status, income, and personal history of cardiovascular disease risk factors (eg, smoking) and time since T2D diagnosis were collected at baseline using a questionnaire.

#### Intervention Preference and Website Usage Data

Preference and usefulness of the Web-based, print [35], email, SMS text messages or telephone call, and postal mail were assessed by asking participants how many times they visited the webpage, read and made references to Shopper’s Guide [35], and how much time they spent on the website or reading the book. In addition, participants were asked which medium they found most helpful and whether the information about the GI concept was informative and helped increase their knowledge and self-efficacy for consuming low-GI foods. Website data measurement programs were built into the website design to compile data points as connections occur with the target audience [56]. Regularly collecting, tracking, and using measurement data makes it possible to understand participants’ characteristics and helps keep the intervention appealing and relevant for achieving the greatest effect [56].

### Statistical Analysis, Power, and Sample Size Rationale

#### Statistical Analysis

Change in the mean daily GI of dietary carbohydrates from baseline to 3 months will be used as our primary effectiveness measure for improved low-GI knowledge and application. Descriptive statistics will be computed for all variables to determine the nature of the data and to test for normality assumptions. Changes in outcomes will be assessed using repeated-measures 2-way analysis of covariance. Potential sociodemographic and clinical factors associated with enhanced GI learning will be evaluated using generalized linear mixed-model analysis. Treatment condition, baseline scores, participant characteristics (eg, sex, education, and income), and computer proficiency that may be significantly related to outcomes will be controlled for. All data will be analyzed using Stata SE 12.1 (StataCorp).

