#### Dietary Assessment, Glycemic Index, and Glycemic Load Estimation

Daily dietary intake was assessed for all participants at baseline and at 3 months using a 3-day food record. The 3-day food records are valid and reliable for capturing dietary behavior change by asking participants to record their food consumption as they eat [37]. All participants were asked to record, in as much detail as possible, descriptions of foods and beverages consumed over a 3-day period (ie, 2 weekdays and 1 weekend day). Participants were given further instructions on how to fill out the 3-day food record. Color photographs were provided to assist participants with estimating and recording appropriate portion sizes of foods and beverages they consumed in the 3-day food record logbooks. Pictures showing sample portions sizes of foods measured against items including a finger, palm of a hand, and a hockey puck were included and participants were encouraged to choose photographs that best represented their portion sizes or specify whether they consumed more or less. Mean daily food consumption and nutrient intake were estimated using the Food Processor Diet Analysis and Fitness Software (ESHA Research) at baseline and 3 months using the Canadian nutrient file.

All carbohydrate-containing foods identified from the 3-day food records were assigned GI values corresponding to the best geographic and botanical matches in the published International Table of Glycemic Index and Glycemic Load Values [33,38] or the updated University of Sydney Web-based database [39,40]. GI values were averaged for foods having more than one GI value from very similar matches. As the International Table and the University of Sydney Web-based databases do not provide an exhaustive entry of glycemic data for every food, the instances where foods could not be matched directly to those in the International Tables or Web-based database, GI values were calculated from the estimated GL [39] or matched to listed foods with similar characteristics (ingredients, composition, and physical properties) based on all information available to [name], a trained dietitian, and from his subjective experience and knowledge of foods [41-43]. As recommended [41,43,44], daily average GI and GL was calculated for all carbohydrate-containing foods identified from the 3-day food records using published international GI tables [33,38] (Figure 1).

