#### Power and Sample Size Rationale

Based on previous studies regarding the efficacy of GI-based nutritional education and glycemic control [14,45] and meta-analysis of studies on low-GI diets and diabetes management [8], an estimated effect size of *d*=1 was set for this intervention. Previous data [46] suggest an SD of GI intake of 4-5 units; thus, an effect size *d*=1 could be achieved with an absolute mean difference of 5 units of GI intake. Given the estimated effect size, 42 participants (21 per arm) would be sufficient for detecting an absolute mean difference of 5 units on the GI intake scale between means with an error of alpha=.05 (2-sided) and beta=.1 (power 1−β=.90; Multimedia Appendix 1); this difference is considered to have significant health benefits from a previous study in which a change of 15 GI units yielded a corresponding HbA_1c_ change of −1.5% [45] and another study in which a change of 4.6 GI units yielded an HbA_1c_ change of −0.25 (95% CI −0.50 to −0.004) [14]. With an estimated attrition rate of 30% (based on the ABCD cohort year 2 participation rate), eligible participants were oversampled (N=67) during recruitment to account for possible loss to follow-up during randomization and intervention periods. This sample size was feasible in view of the dietary assessment (3-day food record) method used to assess food intakes and change in dietary GI, the cost of biochemical and clinical measurements, and the duration of the study.

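### With only two measurement occasions, the arm-by-time contrast of the named repeated-measures model is an unadjusted change-score comparison; a baseline-adjusted ANCOVA would be more precise at no cost

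*Protocol article*

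**What the plan says.** All of the modelling text is in the Statistical Analysis section of the protocol article. It defines the primary measure: "Change in the mean daily GI of dietary carbohydrates from baseline to 3 months will be used as our primary effectiveness measure". It names the method: "Changes in outcomes will be assessed using repeated-measures 2-way analysis of covariance". A separate sentence then gives a second model with a different purpose: "Potential sociodemographic and clinical factors associated with enhanced GI learning will be evaluated using generalized linear mixed-model analysis". The covariate sentence comes last. It lists "Treatment condition, baseline scores, participant characteristics", gives examples and adds computer proficiency, all qualified by "that may be significantly related to outcomes will be controlled for".

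The section on dietary assessment fixes the number of occasions at two: "Daily dietary intake was assessed for all participants at baseline and at 3 months using a 3-day food record".

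The article does not say which model the covariate sentence belongs to, which term of the repeated-measures model is the treatment effect, or whether baseline may have a different slope at each occasion.

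**The concern.** A two-way repeated-measures model for change has arm and time as its factors. With two occasions, one of the two repeated values is the baseline itself. If baseline is then also entered as a covariate, it appears on both sides of the equation. A covariate that is constant within a person drops out of any within-person contrast, so the adjustment that the text appears to promise does not reach the arm-by-time term.

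What is at stake is precision and protection against chance imbalance in a trial of 67 people. Imbalance of that kind is visible in Table 1 (BMI 28.0 against 32.0 kg/m², waist 102.5 against 112.2 cm). Baseline GI by arm is not shown there.

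**Working it through.** **Inputs.** From Power and Sample Size Rationale: difference 5 GI units, SD 4 to 5, two-sided alpha 0.05, power 0.90, 21 per arm, 30% attrition, N = 67. The correlation r is not in the document, so 0.3 to 0.6 is assumed.

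**The plan's own figure.** n per arm = 2(1.960 + 1.282)² × (5/5)² = 21.01. The plan states 21, which is reproduced to within rounding (normal-approximation power 0.8998 at 21 per arm). Expected completers are 67 × 0.7 = 46.9, or about 23 per arm. The SD used is that of the GI level. The SD of a change is SD × √(2(1 − r)), which equals 5 only when r = 0.5.

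**What the model estimates (complete data, one baseline slope).** Let B be baseline GI and Y the 3-month GI.

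1. Arm by time: this contrast depends only on Y − B. The covariate term is the same at both occasions and cancels, so the contrast is the difference between arms in mean change.
2. Arm main effect: this depends on (B + Y)/2. Regressed on arm and B, the B/2 part gives arm a coefficient of zero, and the Y/2 part gives half the ANCOVA coefficient. The standard error is halved too, so t is unchanged.
3. With a baseline-by-time term, the baseline occasion is fitted exactly by B, and arm by time becomes the ANCOVA estimate.

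Least-squares fits to 2000 simulated trials at each of r = 0.3, 0.5 and 0.7 (21 per arm, true effect −5) confirmed all three identities to rounding error (about 1e-13). Mean change-score estimates were −5.02, −5.06 and −5.03, so the contrast is unbiased. Its sampling SD was 1.81, 1.55 and 1.21, against 1.49, 1.34 and 1.13 for ANCOVA.

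**Power at 23 per arm, SD 5, difference 5.** Noncentral t with λ = 5 / (s × √(2/23)); s = 5√(2(1 − r)) with 44 df for the change score, and s = 5√(1 − r²) with 43 df for ANCOVA.

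| r | s, change | λ | power | s, ANCOVA | λ | power | variance ratio (1 + r)/2 |
|---|---|---|---|---|---|---|---|
| 0.3 | 5.92 | 2.87 | 80% | 4.77 | 3.55 | 94% | 0.65 |
| 0.4 | 5.48 | 3.10 | 86% | 4.58 | 3.70 | 95% | 0.70 |
| 0.5 | 5.00 | 3.39 | 91% | 4.33 | 3.92 | 97% | 0.75 |
| 0.6 | 4.47 | 3.79 | 96% | 4.00 | 4.24 | 98% | 0.80 |

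At SD 4 the change score already has 94% power at r = 0.3 and more at higher r. ANCOVA is above it throughout.

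**Chance imbalance.** If the arms differ by D in mean baseline GI, the expected change-score contrast, given that imbalance, is the true effect minus (1 − r)D. One standard error of D at 23 per arm is 5 × √(2/23) = 1.47 units. That shifts the contrast by 0.7 × 1.47 = 1.03 units at r = 0.3, or 0.5 × 1.47 = 0.74 at r = 0.5. ANCOVA removes this shift.

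**Type I error.** In null simulations at 23 per arm, the classical arm-by-time test (a t-test on change) rejects in about 5% of trials. If the model were fitted with a random intercept and baseline as both outcome and covariate, the intercept variance is estimated at zero and the rate rises to about 6.5 to 8.5% for r = 0.3 to 0.6.

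**The case against.** The double use of baseline is an inference. The covariate sentence follows the mixed-model sentence, lists treatment condition as if it were a nuisance variable, and is conditional on significance, so it may govern only the analysis of factors linked to GI learning. The method sentence could also be loose wording for an ordinary baseline-adjusted ANCOVA. A journal article need not list every model term, and a valid change-score test is not an error.

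Much of this stands: the double use is the literal reading, not a certain one. The efficiency point does not depend on it, however. If baseline is absent from the repeated-measures model, arm by time is still the unadjusted change score. Only a baseline-by-time term, or a plain ANCOVA under another name, avoids the loss, and the text states neither.

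A reader might infer two stronger conclusions. The first is that the treatment effect will be reported at half its size. That would happen only if the arm main effect were reported, and the stated measure is change, which points to arm by time. The second is that the test is anti-conservative. That needs a random-intercept version, and the article assigns its mixed model to a different question. The documents support neither for the primary comparison.

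The loss also depends on the inputs: power falls below the planned 90% only with SD near 5 and r below about 0.5.

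**Conclusion.** The concern holds in a limited form. As worded, the primary comparison is most naturally an arm-by-time contrast that equals the unadjusted difference in change. It is valid and unbiased under randomization, but less precise than ANCOVA and exposed to chance baseline imbalance, and the baseline adjustment that the text seems to intend has no effect on it. Over r = 0.3 to 0.6, ANCOVA has 0.65 to 0.80 of the change-score variance. At SD 5 the power gain runs from about 14 percentage points down to about 2; at SD 4 little is at risk.

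These sizes assume complete data on 23 per arm, equal SDs at both occasions, no baseline-by-time term and an r that the documents do not give. The stated sample size is not in error. This is a free improvement and a needed clarification, not a flaw that invalidates the trial.

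**What to change.** Replace the method sentence with wording such as: the primary analysis is a linear regression (ANCOVA) of 3-month mean daily GI on arm with baseline mean daily GI as covariate, and the adjusted arm difference is reported with its 95% confidence interval; continuous secondary outcomes are analyzed in the same form. An acceptable alternative is a constrained longitudinal model in which baseline is an outcome only, with a common baseline mean across arms and no baseline covariate. The covariate sentence should say which model it governs.

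Before analysis the cost is one paragraph; the data are already collected. The article is inconsistent on timing: the abstract's Results and the Summary of Progress to Date say that analysis was completed in December 2018, while Recruitment or Enrollment Status and Timelines describes the database as still being prepared. If the analysis is complete, a silent change of primary model would itself be a problem. The report should then state which term was presented as the treatment effect, keep that result, and give the ANCOVA estimate alongside it, labelled as added afterwards.

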#### Power and Sample Size Rationale

Based on previous studies regarding the efficacy of GI-based nutritional education and glycemic control [14,45] and meta-analysis of studies on low-GI diets and diabetes management [8], an estimated effect size of *d*=1 was set for this intervention. Previous data [46] suggest an SD of GI intake of 4-5 units; thus, an effect size *d*=1 could be achieved with an absolute mean difference of 5 units of GI intake. Given the estimated effect size, 42 participants (21 per arm) would be sufficient for detecting an absolute mean difference of 5 units on the GI intake scale between means with an error of alpha=.05 (2-sided) and beta=.1 (power 1−β=.90; Multimedia Appendix 1); this difference is considered to have significant health benefits from a previous study in which a change of 15 GI units yielded a corresponding HbA_1c_ change of −1.5% [45] and another study in which a change of 4.6 GI units yielded an HbA_1c_ change of −0.25 (95% CI −0.50 to −0.004) [14]. With an estimated attrition rate of 30% (based on the ABCD cohort year 2 participation rate), eligible participants were oversampled (N=67) during recruitment to account for possible loss to follow-up during randomization and intervention periods. This sample size was feasible in view of the dietary assessment (3-day food record) method used to assess food intakes and change in dietary GI, the cost of biochemical and clinical measurements, and the duration of the study.

## Results

### Summary of Progress to Date

Intervention milestones including ethics application, hiring and training of research assistants, and development and pilot-testing of intervention materials ran from July 2016 to October 2017. Data Analysis was completed December 2018.

### Recruitment or Enrollment Status and Timelines

Recruitment and enrollment in the Healthy Eating and Active Living for Diabetes-Glycemic Index (HEALD-GI) trial ran from November 2017 to February 2018. Figure 2 shows the flow diagram detailing the recruitment, screening, random allocation, and baseline and follow-up data collection. Baseline and 3-month follow-up data collection were completed in June 2018. Currently, the study database is being compiled in preparation for performing appropriate analyses and dissemination of findings.

### Participant Characteristics

Overall, 64% (43/67) participants were males; mean age was 69.5 (SD 9.3) years, with a mean diabetes duration of 19.0 (SD 13.7) years, BMI of 30.1 (SD 5.7) kg/m^2^, and HbA_1c_ value of 7.1% (SD 1.2%) (Table 1).

**Figure 2 figure2:**
[figure not shown]
Flow diagram showing participant recruitment and treatment allocation in the Healthy Eating and Active Living for Diabetes-Glycemic Index (HEALD-GI) study.

**Table 1 table1:** Participant characteristics.

Characteristics		All (n=67)	Intervention (n=33)	Control (n=34)
Males, n (%)		43 (64)	20 (61)	23 (68)
Age (years), mean (SD)		69.5 (9.3)	70.7 (9.0)	68.4 (9.6)
**Marital status, n (%)**				
	Married or common law	47 (70)	20 (61)	27 (79)
	Not married (never married, widowed, divorced, or refused to answer)	20 (30)	13 (39)	7 (21)
**Ethnicity, n (%)**				
	Caucasian	62 (93)	30 (91)	32 (94)
	Non-Caucasian	5 (7)	3 (9)	2 (6)
**Education,** **n** **(%)**				
	High school and less	21 (31)	12 (9)	12 (35)
	College and higher	46 (69)	24 (73)	22 (65)
**Employment,** **n (%)**				
	Employed	10 (15)	2 (6)	8 (23)
	Unemployed	5 (7)	1 (3)	4 (12)
	Retired	52 (78)	30 (91)	22 (65)
**Annual household income (Can $), n (%)**				
	<40,000	8 (12)	3 (9)	5 (15)
	40,000-79,999	30 (45)	16 (49)	14 (41)
	≥80,000	20 (30)	7 (21)	13 (38)
	Do not know or refused to answer	9 (13)	7 (21)	2 (6)
Diabetes duration (years), mean (SD)		19.0 (13.7)	20.0 (11.7)	18.0 (15.5)
Glycated hemoglobin value (%), mean (SD)		7.1 (1.2)	7.0 (1.4)	7.1 (0.9)
**Lipid profile, mean (SD)**				
	Total cholesterol (TC; mmol/L)	4.4 (1.0)	4.3 (1.0)	4.5 (0.9)
	HDL (High-density lipoprotein; mmol/L)	1.3 (0.4)	1.4 (0.4)	1.3 (0.4)
	TC/HDL ratio	3.6 (1.5)	3.3 (0.9)	3.9 (1.9)
**Blood pressure (BP; mm Hg), mean (SD)**				
	Systolic BP	127.9 (12.4)	127.7 (9.9)	128.2 (14.6)
	Diastolic BP	70.1 (10.6)	69.8 (8.1)	70.5 (12.8)
Resting heart rate (bpm), mean (SD)		77.8 (14.5)	78.8 (15.3)	76.8 (13.9)
Body mass index (kg/m^2^), mean (SD)		30.1 (5.7)	28.0 (5.1)	32.0 (5.6)
Waist circumference (cm), mean (SD)		107.4 (16.1)	102.5 (15.5)	112.2 (15.4)

## Discussion

### Principal Findings

This protocol outlines the study rationale, design, and evaluation of the HEALD-GI pragmatic randomized controlled trial and reports the baseline characteristics of 67 individuals living with T2D in Edmonton, Alberta, Canada. The HEALD-GI trial was designed to evaluate the effectiveness of Web-based, GI-targeted nutrition education on GI-related knowledge and intakes among adults with T2D.

Major strengths of this trial include the evidence-informed components of the Web-based enhanced, GI-targeted nutrition education including internet chat rooms for peer support and use of email, SMS text messages, and telephone support, which have been shown to enhance the intervention uptake and effectiveness [34,57]. Emails, SMS text messages, and telephone support enable educational content-related exchanges, while chat room platforms in Web-based learning environments enhance social support through creation of relationships that support collaborative learning and sharing of relevant experiences [58-60]. In addition, the involvement of a health professional as a moderator of the Web environment has been shown to enhance Web-based intervention outcomes [57,61]. The provision of “The Shopper’s Guide to GI Values: the Authoritative Source of Glycemic Index Values for More Than 1,200 Foods” [35] also supports preferences for print-based material as a source GI information [25]. This may enhance participant knowledge and self-efficacy for low-GI concept uptake. Use of a 3-day food record method for dietary intake data will help curb recall bias, which is often associated with memory-dependent dietary assessment methods such as 24-hour recall [37].

